### Outcomes

The key outcomes of interest relate to the feasibility of proceeding to a definitive trial. The primary endpoints are therefore based on part 2, and the secondary endpoints relate to part 1 and part 3. Table 3 presents the primary endpoints, and Table 4 presents the secondary endpoints, including the method of assessment, assessment timepoints, and the corresponding study objective.

**Table 3 Tab3:** Primary endpoints based on part 2

Outcome	Assessment procedure	Assessment timepoints	Corresponding study objectives
Feasibility and suitability of trial procedures	Response rates, trial uptake, and number of dropouts	Throughout data collection period	Part 2: objectives 1, 2, and 3
Feasibility of recruitment	Appropriateness of eligibility criteria: number of participants referred or interested who meet the eligibility criteria	Throughout data collection period	Part 2: objectives 1, 2, and 3
	Recruitment rate: number of eligible patients who consent and decline to participate (including reasons for nonparticipation)		
	Retention rates: number of participants who consent and remain in the trial by 6-month follow-up		
Appropriateness of self-report clinical and health economics measures	Completion rates, rate of return, data completeness (the number of missing data), number of reminders and requests for extra support to complete measures, and content of contacts between service providers/researchers and patient participants	Baseline, 3-month and 6-month follow-up	Part 2: objectives 1 and 2
Patient preference for different versions/formats of the outcome data collection tools	Number completed via paper/online/telephone, the number and types of reminders required to complete measures, data completeness, the number of participants who complete 3-month and 6-month follow-up measures	Baseline, 3-month and 6-month follow-up	Part 2: objectives 1 and 2
Fidelity of the intervention	Accuracy and quality of intervention delivery: intervention record forms, audio/video recordings, and case notes of intervention sessions	Throughout data collection period	Part 2: objectives 3, 4, 5, 6, and 7
	Contextual and process issues related to intervention delivery: clinical notes, intervention record forms, audio/video recordings of intervention sessions, and monthly supervision sessions with the NEuRoMS therapists and part 3 interviews		

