**Part 3 — Exploring stakeholder views and experiences**			
Feasibility and acceptability of trial procedures through qualitative data	Interviews will explore patients’ willingness to be randomised; patients’ views on trial recruitment and retention strategies, preferences, barriers, and facilitators to trial recruitment and retention; importance and acceptability of outcome measures	3-month and 6-month interviews with patients and interviews with intervention providers	Part 3 Objective 1
Operational issues in the delivery of cognitive screening and management pathway	Contextual factors which influence intervention and pathway delivery, including mechanisms which influence its affect and outcomes; behavioural elements of the intervention, essential resources needed, and barriers to screening and intervention delivery Reviewing notes from monthly teleconferences/videoconferences with clinicians and supervision sessions with intervention providers and the part 3 interviews	Throughout data collection (notes) 3-month and 6-month interviews with patients and interviews with intervention providers and clinicians	Part 3 Objectives 2, 3, 4, and 6
Patient, intervention provider and clinician experiences of cognitive screening and management pathway	Engagement with the pathway; mechanisms considered important in determining key outcomes: Reviewing notes from monthly teleconferences/videoconferences with clinicians and supervision sessions with intervention providers and the part 3 interviews	Throughout data collection (notes) 3-month and 6-month interviews with patients and interviews with intervention providers and clinicians	Part 3 Objectives 2, 3, 4, and 6
Intervention provider experiences of training	Interviews to explore intervention providers’ readiness to deliver NEuRoMS intervention following training; potential contamination issues; potential improvements to training: reviewing training feedback forms, supervision sessions with intervention providers, and part 3 interviews with intervention providers	Throughout data collection (notes) Interviews with intervention providers	Part 3 Objectives 5 and 6

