### Data collection

Part 1 involves an observational study of those who receive cognitive screening and support, using routinely collected screening data. Observations of how people use and interact with screening will include anonymised usage data (e.g. duration, mode of completion, frequency and type of support received to aid completion, and the reminders required to complete screening) and screening scores from the completed screening tasks from those who gave consent.

Monthly teleconferences/videoconferences between a member of the research team and clinicians at the three MS clinics will also be documented with detailed notes recorded by the researcher and used as a data source. These conversations will explore any problems with implementation, possible solutions, and what is working well and why.

In part 2, once the participant has been recruited and consented, they will complete the demographics form and baseline questionnaires either online, over the phone with a member of the research team, or using postal paper copies. Participants will complete the same questionnaires at 3- and 6-month post-randomisation. Independent researchers, blinded to treatment allocation, will support participants who require help completing the questionnaires over the telephone and will contact participants to complete any missing questionnaire data.

We will keep a record of any intervention contamination. Contamination will be minimised by having only specific intervention providers deliver the intervention for the trial. Intervention providers will be specifically trained to deliver the intervention, and only they will have access to the intervention tools via a password-protected website. The intervention providers will only provide care to intervention group participants and not to control group participants. We acknowledge some contamination may occur if people with MS share information with others, but as the intervention is individually tailored and delivered one to one, the potential for contamination at a participant level is small. Therefore, we will assess to what extent all participants in both control and intervention groups received the NEuRoMS intervention by reviewing clinical notes and service-use questionnaire and through monthly supervision and mentoring sessions and part 3 interviews.

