We will evaluate the use of single work question instead of the full MS Work Difficulties questionnaire [39]. Correlation and reliability analyses will be computed between the total score of the MS Work Difficulties questionnaire and the single question. We will also evaluate the use of the Whooley Questions instead of the full PHQ-9. Correlation analysis will be computed between the total score of the PHQ-9 and the Whooley Questions.

Levels of missing data will be monitored and presented as part of the ongoing data collection, cleaning, and reporting processes. For validated outcome measures where rules are identified for handling missing data, these methods will be implemented. As this is a feasibility study, no further imputation will be applied to the data. Suitability of outcome measures will be determined by the level of completeness. Potential key outcome measures (e.g. Multiple Sclerosis Impact Scale-psychological subscale) for the definitive RCT will be deemed appropriate if minimum success criteria are achieved or if we can identify solutions to overcome any identified issue.

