### Health economics evaluation

The study will explore the feasibility of collecting resource/service use information through the use of the service use questionnaire that was successfully used in a previous study [38]. It was informed by other measures in similar populations or service/setting (e.g. review of Database of Instruments for Resource-Use Measurement website [49]), with a primary focus on collecting direct healthcare and personal social service costs (NHS/PSS perspective) and considering whether direct and indirect non-healthcare costs can be collected to inform a societal perspective. We refined the measure (with PPI and clinician input) to ensure that it reflects good practice [50].

Drawing on previous studies [19, 20], we will consider the outcome domains that stakeholders identify as being relevant and which measures best map across these domains. Justification for the choice of measure (e.g. EQ-5D-5L, ICECAP-A) will be supported by literature searches to ensure our approach is consistent within the field. We will assess the usefulness of instruments by examining descriptive statistics (e.g. completion rates, missing items) with exploration of possible ceiling effects. This assessment, in conjunction with the qualitative data obtained, will be used to finalise the economic outcome measures to use in the definitive trial, including any refinement needed. The outcome for the health economic evaluation will be to derive the framework for a full health economic evaluation for the definitive trial.

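### Suitability of the clinical outcome measures is tied to completeness, with no check of score range and no split between completeness before and after researchers contact participants

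*Protocol article*

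**What the plan says.** The rule is in the protocol article, Statistical analysis: "Suitability of outcome measures will be determined by the level of completeness". The next sentence concerns "Potential key outcome measures (e.g. Multiple Sclerosis Impact Scale-psychological subscale) for the definitive RCT" and says that these "will be deemed appropriate if minimum success criteria are achieved or if we can identify solutions to overcome any identified issue".

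Other sections bear on the same decision:

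- **Data collection:** independent blinded researchers help with telephone completion and "will contact participants to complete any missing questionnaire data".
- **Statistical analysis, on missing data:** "Levels of missing data will be monitored and presented as part of the ongoing data collection, cleaning, and reporting processes".
- **Outcomes, Table 3:** the primary endpoint on appropriateness of the self-report measures covers completion, return and missing data, together with "number of reminders and requests for extra support to complete measures, and content of contacts between service providers/researchers and patient participants".
- **Outcomes, Table 4:** the part 3 interviews cover "importance and acceptability of outcome measures". The Qualitative analysis section allows measures to be refined afterwards, and the Discussion says that feasibility and acceptability data will help settle the final set.
- **Health economics evaluation:** the economic instruments are examined on completion and missing items "with exploration of possible ceiling effects", alongside the qualitative data.

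**The concern.** Part 2 objective 2 in Table 1 names data completeness and the suitability of outcome measures as separate things to assess. The suitability sentence then defines the second by the first. Followed as written, it would pass a scale that everyone completes and on which most participants already have the best score.

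That risk is plausible here. Part 2 enrols people with mild cognitive problems, and the Inclusion criteria set no minimum psychological impact. The example of a candidate key outcome is nonetheless a psychological-impact subscale. Some participants may start with little room to improve. This is an inference, because the article gives no score distribution.

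The second issue is what the completeness figure means. A figure obtained after researchers have followed up gaps describes the instrument plus that effort. A figure at first return describes the instrument alone. The definitive trial needs to know both, and the article does not distinguish them.

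**Working it through.** The suitability rule carries no number and the 60 participants are not derived from a power formula, so there is no stated figure to reproduce. The check is mainly a comparison of sections.

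**Step 1: what each section contributes.**

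| Section | Evidence on measures | Score range for clinical measures? |
|---|---|---|
| Statistical analysis, suitability sentence | Completeness | No |
| Table 3 | Completion, return, missing data, reminders, support, contacts | No |
| Table 4 and Qualitative analysis | Importance, acceptability, refinement | No |
| Discussion | Feasibility and acceptability data | No |
| Outcomes, reasons for choosing the measures | Psychometric properties, as a prior selection reason | Not in this sample |
| Statistical analysis, exploratory analyses | Descriptives, change over time, adjusted differences with 95% intervals | Indirectly; not tied to suitability |
| Health economics evaluation | Completion, missing items, ceiling effects | Economic instruments only |

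No section makes floor or ceiling effects, spread or sensitivity to change a criterion for a clinical measure.

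**Step 2: what a ceiling could cost (illustration).** Let c be the share already at the best score. Assume that they contribute zero change and that the SD is unchanged. The mean effect is multiplied by (1 − c). Required sample size varies with the inverse square of the effect, so it is multiplied by 1/(1 − c)²:

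- c = 10%: 1/0.9² = 1.23
- c = 20%: 1/0.8² = 1.56
- c = 30%: 1/0.7² = 2.04

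The values of c are assumed. Scores piled up at one end usually also have a smaller SD, so these factors may be too large.

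**Step 3: what contact could do to completeness (illustration).** Let p be completeness at first return and r the share of gaps recovered. Completeness afterwards is p + (1 − p)r. Both inputs are assumed.

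| p | r = 25% | r = 50% | r = 75% |
|---|---|---|---|
| 60% | 70% | 80% | 90% |
| 70% | 77.5% | 85% | 92.5% |
| 80% | 85% | 90% | 95% |

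For example, 0.60 + 0.40 × 0.75 = 0.90. Under these assumptions, contact moves the figure by 5 to 30 percentage points.

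**Step 4: precision available.** With 60 participants, an observed 80% complete (48/60) has a Wilson 95% interval of 68.2% to 88.2%. By symmetry, 20% at the best score (12/60) has 11.8% to 31.8%. The trial can reveal a gross ceiling but cannot estimate a ceiling rate closely.

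**The case against.** The strongest reply is that the article as a whole does not rely on completeness. Table 3 records the burden of completion, the interviews ask about importance and acceptability, and good psychometric properties were a reason for the initial choice. The planned descriptive and change analyses would probably expose a scale with most people at its best score. All of this stands, so a reader who infers that completeness is the only evidence in the study goes too far. What remains is that none of this evidence is a score-range criterion, and the suitability sentence refers to none of it.

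Three other stronger readings are also unsupported:

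- **Completeness is counted only after gaps are chased.** The order is not stated. Missing data are monitored as collection proceeds, and reminders and support requests are recorded. If the definitive trial keeps the same follow-up, the figure after contact is the relevant one for its planning. Only the lack of a stated distinction stands.
- **A measure cannot fail.** One with a problem and no identifiable solution does fail. Repairing a measure and proceeding is ordinary in feasibility work. The minimum success criteria may be set in the analysis plan, which is not shown, so their absence here is no finding.
- **The rule will select an uninformative primary outcome.** The article does not say that this sentence alone selects the definitive trial's primary outcome.

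It may also be said that the matter belongs in the analysis plan. Details do, but this article states a criterion, and the criterion as stated is too narrow for the objective it serves.

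**Conclusion.** The point holds in limited form. For the clinical measures, the suitability sentence rests on completeness, which is no evidence of room to change. The article applies a ceiling check to the economic instruments and gives no reason for leaving the clinical ones out. Completeness before and after researchers' contact is not distinguished.

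The consequence is possible rather than demonstrated. The inflation factors of 1.23 to 2.04 depend on assumed ceiling rates of 10% to 30% and a fixed SD. The shifts in completeness depend on assumed first-return and recovery rates. No figure in the documents shows that any candidate measure has a ceiling problem. The point is still worth acting on, because it bears on a named objective and the data needed are already being collected.

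**What to change.** Amend the suitability sentence in Statistical analysis, and carry it into the analysis plan, so that each candidate key clinical measure, such as the psychological subscale of the Multiple Sclerosis Impact Scale, is judged on:

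1. completeness, reported at first return and separately after researchers' contact;
2. the percentage at floor and at ceiling, and the SD, at baseline and follow-up, extending to clinical measures the ceiling check planned for the economic instruments (EQ-5D-5L and ICECAP-A are the article's examples);
3. the burden data in Table 3 and the interview data on importance and acceptability in Table 4.

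The 80% and 50% cut-offs should not be borrowed for completeness, because the article sets them for retention. With about 60 participants, floor and ceiling percentages should be read with their intervals.

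The cost is a few extra columns in descriptive tables that are already planned, plus a marker for whether each questionnaire's data came at first return or after contact. No new assessments are needed. The article says that the analysis plan will be agreed before data collection is completed. The marker, however, has to be in place while questionnaires are being returned.

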### Qualitative analysis

Qualitative data from part 3 will be analysed using a framework approach [47, 48] using QSR NVivo. Data will be coded by research team members, and the coded data will then be mapped to thematic matrices which reflect resources required for cognitive screening and management pathway to be delivered, contextual factors which influence its delivery, mechanisms which influence its affect, and outcomes which are described by participants. This will enhance our understanding of the key issues for stakeholders in relation to screening, intervention, and trial procedures. It will allow us to explore the behavioural elements of the intervention, essential resources, and barriers to screening and intervention delivery and trial procedures. If required, the framework will be revised to include new concepts introduced during the interviews, with input from PPI team members. Once all the data are mapped onto the framework, tables will be used to summarise each main theme. Interpretation of this data will inform a final revision of the logic model and programme theory and the design of the definitive trial. Intervention documents, training package, and outcome measures will be refined as necessary.

### Health economics evaluation

The study will explore the feasibility of collecting resource/service use information through the use of the service use questionnaire that was successfully used in a previous study [38]. It was informed by other measures in similar populations or service/setting (e.g. review of Database of Instruments for Resource-Use Measurement website [49]), with a primary focus on collecting direct healthcare and personal social service costs (NHS/PSS perspective) and considering whether direct and indirect non-healthcare costs can be collected to inform a societal perspective. We refined the measure (with PPI and clinician input) to ensure that it reflects good practice [50].

Drawing on previous studies [19, 20], we will consider the outcome domains that stakeholders identify as being relevant and which measures best map across these domains. Justification for the choice of measure (e.g. EQ-5D-5L, ICECAP-A) will be supported by literature searches to ensure our approach is consistent within the field. We will assess the usefulness of instruments by examining descriptive statistics (e.g. completion rates, missing items) with exploration of possible ceiling effects. This assessment, in conjunction with the qualitative data obtained, will be used to finalise the economic outcome measures to use in the definitive trial, including any refinement needed. The outcome for the health economic evaluation will be to derive the framework for a full health economic evaluation for the definitive trial.

### Data management

All data will be handled confidentially and will be anonymised or pseudonymised (as appropriate) and be kept separate from information about the identity of the participants and documents with patient identifiable data. Each participant will be assigned a unique identity number for use on case report forms, other study documents, and electronic databases. Electronic data including study databases will be held securely and password protected on secure university networks. Paper records will be held securely, in locked rooms and cabinets. Paper records will be entered onto electronic databases by research team. Accuracy of data entry will be checked by a member of the research team who did not complete the original data entry.

### Governance

The study will be overseen by an independent programme steering committee, with an independent chair, expert clinician and researcher, statistician, and PPI representative. The study sponsor is the Nottinghamshire Healthcare NHS Foundation Trust. The study will be managed and coordinated by the programme management group, which consists of the chief investigator, programme manager, PPI coinvestigators, and other co-applicants and researchers involved with the NEuRoMS project.

### Patient and public involvement

This protocol has been developed in conjunction with our PPI coinvestigators (who have MS) and our local MS-PPI group. Our PPI coinvestigators have been involved with every key stage of the research process from identifying research questions, guiding funding applications, developing and testing the cognitive screening technology and protocol development, and informing study design. All patient-facing material has been co-written with, and approved by, our PPI partners.

We will continue to work closely with our MS PPI group to ensure we produce useful findings that can facilitate the transferability of the screening and management pathway into practice in a range of healthcare settings. Our PPI coinvestigators and our PPI group will continue to be involved with every key stage of the research process (e.g. data collection, analysis, write up, and dissemination) providing us with the real-life experiences of living with MS and what they feel is needed.

### Dissemination

Study findings will be disseminated to scientific audiences, people with MS, policymakers, healthcare networks, relevant organisations, and stakeholders. Study findings will be published in peer-reviewed journals, presented at national and international conferences, and made available to relevant patient groups via a range of dissemination channels. Our PPI coinvestigators will also disseminate research findings to the wider MS community and public through local and national networks (e.g. local support groups, newsletters) and through social media and other media channels. Participants will be provided with a lay summary of the findings (produced in consultation with our PPI coinvestigators and PPI group), and the summary will be made available on the NEuRoMS study website. Authorship on publications will be based on the International Committee of Medical Journal Editors Recommendations for the Conduct, Reporting, Editing, and Publication of Scholarly Work in Medical Journals [51].

